## Abstract

**Background:**

Myopia has emerged as a major threat to the visual health of adolescents worldwide. Early intervention can effectively slow down the progression of myopia in adolescents. *Tuina* (also known as Tui Na), a significant therapeutic method in traditional Chinese medicine, has shown promising clinical efficacy in delaying the progression of myopia; however, it lacks robust, large-scale, and standardized randomized controlled trials.

**Objective:**

This study aims to explore the efficacy and safety of *tuina* therapy in managing myopia in adolescents, thereby providing solid evidence for the application of *tuina* in the clinical treatment of myopia.

**Methods:**

This study is a multicenter randomized controlled clinical trial. A total of 62 children with myopia will be recruited from 4 hospitals and randomly assigned in a 1:1 ratio to a *tuina* experimental group and a drug-positive control group (tropicamide eye drops). Treatments in each group will be administered 3 times per week for a total of 8 weeks. The *tuina* experimental group will receive 20 minutes of *tuina* therapy per session, while the drug-positive control group will receive tropicamide eye drops administered every other day, with 2 drops per session. The primary outcome measures include uncorrected visual acuity and axial length, while secondary outcome measures include refractive power and accommodative amplitude. Data will be collected at baseline (week 0), on the day of completion of weeks 4 and 8 of treatment, and at the end of the 10-week follow-up period. Adverse events will be monitored and recorded throughout the study. Statisticians will be blinded. Data will be analyzed using SPSS version 28.0.

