## Methods

### Study Design

This study is designed as a multicenter randomized controlled noninferiority trial to be conducted from June 2025 to October 2026. We plan to recruit 62 participants from 4 hospitals in Yunnan Province. Eligible participants will be randomly assigned in a 1:1 ratio to the *tuina* experimental group and the positive drug control group (tropicamide eye drops). Each participant will undergo an 8-week treatment period followed by a 2-week follow-up. Baseline information and outcomes will be assessed at baseline, at the completion of weeks 4 and 8 of treatment, and at the end of the 10-week follow-up (Figure 1). This trial adheres to the guidelines of the SPIRIT (Standard Protocol Items: Recommendations for Interventional Trials).

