### Sample Size

Using G*Power software to calculate the sample size, based on the preliminary pilot study results, the expected efficacy rate in the manipulation treatment group is above 80% (*P*<.05). Therefore, we set an expected effect size of 0.8. To detect between-group differences with 80% statistical power (*β*=.20), we choose a 2-tailed α level of .05. With an allocation ratio of 1:1, the required sample size was 52 participants (26 per group). Considering a 20% expected dropout rate, the final sample size was set at 62 participants (31 per group).

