### Outcomes Measures

#### Primary Outcome

##### Uncorrected Visual Acuity

We use an international standard visual acuity chart to assess visual acuity, record uncorrected visual acuity (UCVA) results in decimal notation, and subsequently convert them into logMAR format for statistical purposes. The complete disappearance of symptoms such as visual fatigue and exotropia, the restoration of distant vision, and the achievement of a visual acuity of 5.0 on the visual acuity chart are indicative of a cure; the basic disappearance of symptoms with an improvement of 3 to 5 lines on the visual acuity chart is indicative of marked efficacy; a significant alleviation of symptoms with an improvement of 2 lines on the visual acuity chart is indicative of efficacy; no change in symptoms with an improvement of 1 line on the visual acuity chart is indicative of inefficacy. The brightness of the visual acuity chart box must meet the latest national standards, which stipulate that the brightness of the visual acuity chart box should not be less than 200 cd/m^2^. We check the brightness of the examination room, as it affects the size of the pupil and use moderate appropriate lighting, with a diameter of the pupil around 3 mm being optimal.

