##### Axial Length

We measure AL using ophthalmic A-ultrasound, obtain 5 readings with differences between them all less than 0.05 mm, and take the average. Normal AL for adolescents ranges from 22 to 24 mm, and values outside this range represent refractive errors.

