### Data Analysis

All data will be analyzed using SPSS version 28.0 and GraphPad Prism version 10.3.1 statistical software. For normally distributed data, results will be described as mean (SD) and analyzed using the *t* test. For nonnormally distributed data, results will be described as median (IQR) and analyzed using the Wilcoxon rank sum test for within-group comparisons and the Mann-Whitney *U* test for between-group comparisons. A 2-sided *P* value of .05 will be considered statistically significant. Missing data will be handled using expectation maximization, last observation carried forward, or listwise deletion.

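### Two unranked primary outcomes at three visits, with no success rule and one unadjusted .05, do not match a sample size planned for a single comparison; the UCVA grading also has gaps

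*Protocol article*

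**What the plan says.** **Outcomes.** The Abstract (Methods) says that "The primary outcome measures include uncorrected visual acuity and axial length", and the outcome sections list both under the primary heading without ranking them. It is not said whether success on one is enough or both are needed.

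**Visits.** Study Design has outcomes assessed at baseline, "at the completion of weeks 4 and 8 of treatment, and at the end of the 10-week follow-up". That gives three post-baseline visits (weeks 4, 8 and 10), none called primary.

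**Threshold.** Data Analysis plans t tests or rank tests, and a 2-sided P "value of .05 will be considered statistically significant". The same threshold applies throughout.

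**Sample size.** The Sample Size section uses one effect size of 0.8, not tied to either outcome. It plans "To detect between-group differences with 80% statistical power" and states "we choose a 2-tailed α level of .05", giving 26 per group. The effect size is justified by an expected efficacy rate above 80%.

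**Two forms of UCVA.** Examiners are to "record uncorrected visual acuity (UCVA) results in decimal notation, and subsequently convert them into logMAR format for statistical purposes". The same paragraph then defines four grades that combine symptoms with chart lines gained. At the top, the disappearance of symptoms, restored distance vision and "the achievement of a visual acuity of 5.0 on the visual acuity chart are indicative of a cure". The lower grades need a gain of 3 to 5 lines, 2 lines or 1 line, each with its own symptom condition; the 1-line grade is the one called inefficacy.

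**The concern.** The article sets up six between-group tests on primary outcomes (two outcomes by three visits) but sizes the trial for one. Without a rule for what counts as success, any of the six could be put forward as the primary result. That raises the false-positive risk if any win counts, and lowers power below the stated 80% if both outcomes must succeed.

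The grading raises a second problem. It is the only definition of efficacy grades in the article, and the sample size is argued from an efficacy rate. As written, some possible results have no grade, and the cut-off for the top grade is in a notation that is not reconciled with the recording or the analysis.

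**Working it through.** **1. The plan's own figure.** Inputs from Sample Size: d = 0.8, 2-tailed alpha .05, power 80%, 1:1 allocation. A two-sample t test (noncentral t) gives n = 25.52, so 26 per group and 52 in total, with power 80.7%. The stated 52 is reproduced, but only for one comparison at the full .05.

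**2. Error if any of six tests counts (assumed rule).** For independent tests the chance of at least one P<.05 under no difference is 1 − 0.95^6 = 0.265. Visits on the same child are correlated and the article gives no correlations, so they were varied in a multivariate-normal simulation (400,000 draws), with 0 to 0.5 between outcomes:

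| Correlation between visits (assumed) | At least one 2-sided P<.05 | At least one of six in tuina's favour, one-sided .025 |
|---|---|---|
| independent tests | 26.5% | 1 − 0.975^6 = 14.1% |
| 0.5 | 22–23% | 11–12% |
| 0.8 | 17–19% | 9–10% |
| 0.9 | 15–16% | 7–8% |
| 0.95 | 13–14% | about 7% |

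The last column is the relevant one for a noninferiority claim and compares with a nominal 2.5%. The graded form of UCVA is not counted in any of these figures.

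**3. Error at one named visit, either outcome sufficient.** 1 − 0.95^2 = 0.0975 if independent; 8–10% with correlations up to 0.7 between outcomes.

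**4. Both outcomes required at one visit.** Error does not inflate: when neither outcome has an effect, both favour tuina in fewer than 0.5% of trials. If each test has 80% power, joint power is 0.80 × 0.80 = 0.64 when the outcomes are independent and 0.73 at a correlation of 0.8 (bivariate normal).

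**5. Alpha split between two outcomes at one visit.** At .025 each, 26 per group has 71.6% power. Reaching 80% needs 31 evaluable per group (62 in total), which is the whole planned enrolment before dropout. With 20% dropout it is 62/0.8 = 77.5, so 78.

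None of these rules for two outcomes delivers both 5% error and 80% power at 26 per group. A single named endpoint and visit does.

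**6. The grading, read against itself.** The following have no grade:
- no change in acuity, because the lowest grade requires a 1-line gain;
- worsening;
- a gain above 5 lines that falls short of cure;
- a line gain without the symptom relief attached to that grade.

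The cure value of 5.0 is tied to the chart, while acuity is recorded as a decimal and analysed as logMAR. No conversion or notation is stated for it.

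**The case against.** The article is a condensed account, and an analysis plan not shown may contain a multiplicity procedure. That is fair for the procedure's details. It does not remove the mismatch, because the article itself fixes two primary outcomes, three visits, one threshold and a sample size that holds for one comparison.

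A reader might infer that the trial's false-positive rate simply is 15–26%. The article does not support that: it states no any-win rule and no correlations, and the figure is a 2-sided rate while Study Design declares noninferiority. The Expected Findings text, which anticipates noninferior results on all four measures, reads more like a conjunction than any of six, though it is not a decision rule. The objection to a flat figure stands, so every percentage here is conditional.

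It can also be said that logMAR is the form named for statistical use, so the grading may never be tested. That stands too. The grading is therefore a separate defect of definition, not a further source of error inflation.

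Three other inferences go too far:
- **Reading 5.0 as a decimal acuity, and so as an absurd cut-off.** The article does not say that it is a decimal value. The defect is the unstated notation.
- **Claiming that many children could not be graded.** There are no data on how many would fall into the gaps.
- **Arguing that axial length is too imprecise to be primary, because examiners "obtain 5 readings with differences between them all less than 0.05 mm".** That tolerance applies between single readings, whereas the average of five is used. The article gives neither a growth rate nor an SD of change.

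**Conclusion.** The point holds in conditional form. The primary endpoint, primary visit and success rule are left open, and the stated sample size fits only one comparison. If any of six wins counts, the chance of a false 2-sided finding is at most 26.5%, about 15–16% at an assumed visit correlation of 0.9, and 8–10% at a single visit. For one-sided noninferiority claims at .025 it is about 7–14% against 2.5%; as the article gives no margin, this cannot be tied to a specific test. If both outcomes must succeed at one visit, the cost is power (about 64–73%, assuming 80% for each test), not error.

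The gaps in the grading and the unreconciled cure notation follow from the text alone and rest on no assumption.

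The Results section already reports, at 29 enrolled, that the data favour tuina on both UCVA and axial length. A reader might infer that the choice of endpoint has been driven by the data. The article does not show that, but it makes it important to settle the choice now and openly.

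**What to change.** Name one primary endpoint and one visit. Week-8 logMAR UCVA is an example, since logMAR is the form the article assigns to statistical use. Test week-8 axial length next, at the same alpha, only if the first test succeeds. Define success for each in terms of the declared noninferiority design. Label weeks 4 and 10 supportive.

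Make the efficacy grading descriptive. Alternatively, rewrite it as an exhaustive rule on the recorded scale, so that every possible result has exactly one grade and the cure value is stated in that scale.

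Make the choice without reference to data by arm, and disclose that impressions on both outcomes have already been reported.

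The cost is wording in the protocol and analysis plan. A single primary test keeps the full .05 that the stated 26 per group assumes; whether d = 0.8 suits a noninferiority comparison is a separate question. The downside is that axial length can be claimed only if UCVA succeeds. If the sponsor prefers both outcomes to count, the sample size should be recalculated for that rule.

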**Results:**

This study has been funded, and recruitment began in June 2025. As of December 2025, 29 participants have been enrolled, with 16 allocated to the *tuina* group and 13 to the drug-positive control group. Recruitment is expected to continue until October 2026. Final manuscript submission is anticipated by December 2026.

**Conclusions:**

This study aims to evaluate the efficacy and safety of *tuina* therapy in the treatment of adolescents with myopia. We hypothesize that the therapeutic effect of *tuina* therapy is noninferior to that of tropicamide eye drops, with the additional advantages of fewer side effects and stable long-term efficacy, thereby providing reliable evidence and support for the application of *tuina* therapy in the management of myopia in adolescents.

## Introduction

### Background

Myopia, a common ocular disorder predominantly developing during childhood and adolescence, is characterized by excessive elongation of the eye globe, leading to the focusing of distant object images in front of the retina and thereby causing blurred distance vision. With continuous advancement of socioeconomic levels [1], the widespread prevalence of mobile electronic devices [2], and a lack of outdoor activities [3], the problem of myopia among adolescents has become increasingly severe. Currently, the global population with myopia is approximately 2 billion individuals (28.3% of the global population), and it is estimated that by 2050, the prevalence of myopia will increase to 4.76 billion individuals, approximately half of the global population [4]. Among school-aged children (6‐19 y old), the prevalence of myopia in East Asian regions is the highest (73%), which is significantly higher than that in other regions of the world, including North America (42%), Europe (40%), South America (10%), and Africa (3.4%‐4%) [5]. Taking China as an example, more than 80% of high school students suffer from myopia [6], which not only has a significant impact on children’s academic performance and future career choices [7] but also serves as a major cause of incurable vision impairments, such as glaucoma, retinal detachment, and macular degeneration [8]. Owing to the extremely high prevalence rate, myopia has caused tremendous losses to socioeconomic development. A research report stated that in 2019, productivity loss caused by severe visual impairment and blindness was approximately US $94.5 billion, and it is expected to rise to US $229.3 billion by 2050 [9]. Therefore, researchers and clinicians are eager for effective treatment methods that can delay or even prevent the progression of myopia in children.

Currently, common interventions for myopia include surgical and nonsurgical methods. Refractive surgery is used to correct the vision; however, high costs [10] and postoperative complications, such as dry eye syndrome, are drawbacks that are difficult to ignore in surgical treatments [11]. Nonsurgical interventions include pharmacological and nonpharmacological treatments, with pharmacological therapy commonly using low-concentration atropine; however, photophobia [12] and dry eye syndrome are common complications. Tropicamide eye drops are a cholinergic receptor antagonist medication. Compared with atropine, tropicamide has the advantages of rapid metabolism, fewer adverse reactions, higher safety, and higher patient compliance and adherence. Evidence suggests that, compared with atropine treatment, tropicamide eye drops can improve the clinical treatment outcomes and enhance the quality of life in adolescents with myopia [13].

Optical therapies, such as myopia-control glasses, including highly aspheric lenslets, spectacle lenses with slightly aspheric lenslets, and single-vision spectacle lenses, are widely applied methods for myopia control and can effectively slow the progression of myopia and axial elongation [14]. However, a large-scale network meta-analysis indicated that the GRADE (Grading of Recommendations Assessment, Development, and Evaluation) evidence level for myopia-control spectacles is relatively low, and their true efficacy requires further investigation [15]. Corneal reshaping lenses can correct myopia to some extent but are associated with adverse reactions, such as corneal infections [16], and many children find these lenses difficult to tolerate. Some studies have shown that more than half of children were unable to complete the treatment [17]. Moreover, high costs necessitate long-term consideration when choosing contact lenses. A study on the cost of myopia treatment over 5 years found that corneal reshaping lenses were the most expensive, with an approximate cost of US $15,347 [10]. Recent research has found that repetitive low-intensity red light therapy can help improve axial length (AL), control vision in children with high myopia, and increase macular choroidal thickness [18]; however, there is still a certain rebound effect after the cessation of repetitive low-intensity red light treatment [19].

*Tuina* (also known as Tui Na), one of the nonpharmaceutical therapies characteristic of traditional Chinese medicine (TCM), can be traced back to the Qin and Han dynasties (99 BC-26 BC) [20,21] and has a history of more than 2000 years. Massage, acupressure, acupoint eye exercises, and other techniques all fall under the category of *tuina*. Existing research has demonstrated that localized *tuina* therapy around the eyes can promote meridian circulation, enhance blood circulation, and alleviate spasms of the ciliary and extraocular muscles [22-24]. These effects may be associated with improvements in retinal thickness, choroidal thickness, perfusion area, and vascular density through acupoint massage around the eyes [25]. Tian et al [26] evaluated the impact of eye exercises on AL in adolescents and found that the frequency of eye exercises was conducive to controlling the trend of axial elongation. Moreover, a large-scale meta-analysis suggested that acupoint stimulation around the eyes has a moderate protective effect in controlling myopia; however, incorrect execution and attitudes may have a negative impact on vision health [27]. This indicates that the correct method of stimulating ocular acupoints is of paramount importance for the recovery of vision.

The holistic concept of TCM emphasizes the dialectical relationship between local functions and the whole body, with the various parts of the human body being inseparable in structure and mutually influential in function. Normal vision is a result of the proper functioning of all organs. A sole focus on local manipulation neglects the holistic perspective of TCM, potentially affecting the final clinical efficacy. Therefore, we have developed an integrative approach combining overall regulation with local treatment, known as selective spinal *tuina* manipulation therapy, as a potential intervention for myopia in adolescents. However, high-quality medical evidence supporting this approach is currently lacking.

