### Objectives

This study aims to conduct a high-quality randomized controlled trial to objectively evaluate the efficacy and safety of selective spinal *tuina* manipulation therapy in the treatment of childhood myopia. We hypothesize that selective spinal manipulation therapy can improve vision in children with myopia and is safer than drug therapy, with no side effects and more stable long-term efficacy.

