#### Drug-Positive Control Group

The positive-drug control group will receive treatment with compound tropicamide eye drops (Shenyang Xingqi Co., Ltd.; product specification: 1 ml per vial) at a frequency of once every 2 days before bedtime, with 2 drops per administration. The group will continue the treatment for a duration of 8 weeks.

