### Conclusions

This study will investigate the efficacy and safety of *tuina* therapy in the prevention and treatment of myopia in adolescents, providing evidence for clinical decision-making and supporting the inheritance and development of *tuina* therapy. It is noteworthy that previous studies have not investigated the intervention effects of *tuina* therapy on myopia from the perspective of TCM holistic philosophy. This study will be the first to explore the effects of *tuina* therapy on myopia in adolescents from the perspective of TCM holistic philosophy. This study could support *tuina* therapy as an effective method for managing myopia in adolescents, offering potential benefits to patients and their caregivers.

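### With no untreated or sham arm, and no benefit of the drops over no treatment documented in the article, noninferiority supports only a claim relative to the drops, not that tuina is effective

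*Protocol article*

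**What the plan says.** - **Design.** Study Design calls this a "multicenter randomized controlled noninferiority trial". Randomization and Blinding gives two interventions, and Innovations and Limitations confirms that a sham group was left out because blinding is difficult. No untreated or placebo arm is described.
- **Endpoints.** The Abstract (Methods) states: "The primary outcome measures include uncorrected visual acuity and axial length".
- **Support for the comparator.** Background says that, "compared with atropine treatment, tropicamide eye drops can improve the clinical treatment outcomes", and adds quality of life. Of atropine, the reference drug in that sentence, it says only "pharmacological therapy commonly using low-concentration atropine" and lists complications.
- **Product.** The Abstract, Background and Study Design speak of tropicamide. Drug-Positive Control Group gives "compound tropicamide eye drops".
- **Claims.** Objectives sets out to "objectively evaluate the efficacy and safety of selective spinal" tuina and hypothesises that the therapy improves vision. Results reports that the data from 29 enrolled children already point to tuina as an alternative that works. Conclusions says the study could support tuina "as an effective method for managing myopia in adolescents".

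**The concern.** A noninferiority comparison shows that a new treatment is not worse than the control by more than a margin. It shows that the new treatment works only if the control, as given in the trial, is known to beat no treatment on the same endpoints over a similar period, and if the margin is smaller than that benefit. Without that link, two treatments with no effect would be noninferior to each other.

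The article makes absolute statements about tuina but does not document the link. A finding of no worse than the drops could then be published as evidence that tuina improves vision or controls myopia.

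Within-arm change cannot fill the gap. Data Analysis plans within-group tests, and Results already reads change during the trial as benefit. Without a concurrent untreated group, such change includes the passage of time. For UCVA it also includes practice with the chart and expectation in families who know the treatment. (Chart practice does not apply to AL measured by ultrasound.)

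**Working it through.** **1. What a claim of efficacy needs, and what the article gives**

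| Needed | Given in the article |
|---|---|
| Control compared with no treatment or placebo | One sentence, against atropine (Background) |
| Result on UCVA or AL | Unspecified clinical outcomes and quality of life |
| Size of the control's effect | None |
| Indirect route: atropine's effect on UCVA or AL | None; only that it is commonly used, with complications |
| Same product as in the trial | Tropicamide in Background; compound tropicamide in Drug-Positive Control Group |
| Concurrent untreated or sham group | None |

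Each link from noninferior to effective is undocumented in this article. The statements in Objectives, Results and Conclusions are absolute, and the comparison is relative.

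**2. The plan's own sample size**

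Inputs (Sample Size): effect size 0.8, two-sided alpha 0.05, power 80%, 1:1 allocation. A two-sample t test gives n = 25.52, so 26 per group and 52 in total, with 80.7% power. The stated 52 reproduces. It is a calculation for detecting a difference. It contains no margin and no effect of the control over no treatment, so it cannot supply the missing link.

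For scale, assume a true difference of zero and one-sided alpha 0.025. With 26 per group, SE = SD × √(2/26) = 0.277 SD and power = Φ(margin/SE − 1.96):
- margin 0.5 SD: Φ(1.803 − 1.96) = 44%
- margin 0.8 SD: Φ(2.884 − 1.96) = 82%

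So 52 evaluable children give about 80% power only with a margin near 0.8 SD. Nothing in the article shows that the drops' own effect on UCVA or AL is that large.

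**3. Illustration for AL**

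The inputs are assumptions, not figures from the article: untreated growth of 0.2–0.6 mm/year, and a control that slows it by 30–50%.

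Benefit of the control over no treatment = annual growth × (weeks/52) × proportion slowed.

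| | 8 weeks | 10 weeks |
|---|---|---|
| Growth at 0.2 mm/year | 0.2 × 8/52 = 0.031 mm | 0.2 × 10/52 = 0.038 mm |
| Growth at 0.6 mm/year | 0.6 × 8/52 = 0.092 mm | 0.6 × 10/52 = 0.115 mm |
| Lowest benefit (0.2 mm/year, 30%) | 0.009 mm | 0.012 mm |
| Highest benefit (0.6 mm/year, 50%) | 0.046 mm | 0.058 mm |

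A margin would have to be smaller than these amounts before AL noninferiority said anything about slowed growth. No comparable illustration is offered for UCVA, because the article gives nothing to build one on.

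**The case against.** **The source is unseen.** Background cites a study for the tropicamide sentence. That study may report UCVA or AL, and the full protocol may hold a fuller rationale. This stands, so the point is limited to what this article documents. A reader might infer that tropicamide does not work; the documents do not support that. They are silent on its effect over no treatment.

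**The claims are partly hedged.** Objectives says evaluate, Conclusions says could support, and Results says suggesting. The Abstract (Conclusions) and Expected Findings state the expectation relative to the drug. This lowers the severity. It does not remove the absolute hypothesis in Objectives, the statement in Results drawn mid-trial (29 of 62 children, 47%), or the use of the word effective in Conclusions.

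**The AL argument can be pushed too far.** Axial Length requires the operator to "obtain 5 readings with differences between them all less than 0.05 mm". A reader might infer that a margin of about 0.05 mm would be met by no treatment at all, or that an untreated child would look noninferior. The documents do not support that:
- The article states no margin. The 0.05 mm is a tolerance between readings that are then averaged, which is a different quantity from a between-group difference in mean change.
- Noninferiority is judged on a confidence bound. With an 8-week deficit of 0.046 mm, the bound stays under 0.05 mm only if SE < (0.05 − 0.04615)/1.96 = 0.0020 mm. With 26 per arm that means an SD of change below 0.0020/0.277 = 0.007 mm. At the low end (0.009 mm) the limit is (0.05 − 0.00923)/1.96/0.277 = 0.075 mm. The article gives no SD.
- The highest 10-week value, 0.058 mm, already exceeds 0.05 mm.

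**The product name is a separate matter.** The inconsistency does not by itself prove the point. It does mean that the cited evidence cannot yet be tied to the product given.

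**Conclusion.** The point holds as a limit on what may be concluded, and should be fixed. On the article's own text, a noninferiority result would support a statement about tuina relative to the drops and no more. This rests on three readable facts: there is no untreated, placebo or sham arm; the only comparator evidence is against atropine and names neither UCVA nor AL; and some of the stated claims are absolute. No calculation is needed for it.

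The AL figures (0.009–0.046 mm at 8 weeks, 0.012–0.058 mm at 10 weeks) depend wholly on the assumed growth and slowing. They show only that AL noninferiority over this period would be weak evidence of slowed growth unless the margin were smaller than the control's benefit.

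**What to change.** 1. Word the Abstract (Conclusions), Objectives, Results and Conclusions so that the trial concludes on tuina relative to the named drops.
2. Remove the mid-trial efficacy statement from Results.
3. State that within-arm change is descriptive and is not evidence of efficacy.
4. State that AL noninferiority at 8–10 weeks will not be read as evidence of slowed axial growth.
5. Reconcile tropicamide (Abstract, Background, Study Design) with compound tropicamide (Drug-Positive Control Group), and use one product name wherever the comparison is stated.

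The cost is wording only, with no added arm, children or measurements. The downside is a narrower claim.
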